### Program feasibility

Intervention implementation data are assessed through either participant’s self-report in the paper questionnaire (i.e., treatment of text messages, use of MobileMums refrigerator magnet) or through objective tracking of delivery data (i.e., duration of initial counselling session, number of text messages sent/received, number of goal check text message responses received, number of Facebook^©^ posts, and website usage).

### Program acceptability

Participants’ recall of, use and satisfaction with the program are assessed using self-report items used previously by the investigators [10,27]. Participant responses to the goal check text messages, any unprompted text messages sent by participants, and any additional communication with the behavioural counsellor was monitored [27]. Participants are also asked to describe the MobileMums program in one sentence to provide an unfettered qualitative assessment of the program.

### Cost-effectiveness

Participant-reported use of health care services is assessed in the telephone interview at each data collection point. Participants were asked if they have had any consultations for: their own health with various health professionals; any visits to accident and emergency department; visits by home health nurses; hospital admissions (plus length of stay); and, any other costs associated with taking up any form of physical activity. Costs associated with any reported health service use will be estimated from the Commonwealth Government schedule of re-imbursements [33]. Additional costs associated with program delivery (e.g., computer/database, print materials, text messages, behavioural counsellor time, and other staff costs) were monitored by research staff. Health benefits are collected in the self-administered paper questionnaire at each data collection point using the SF-12v2™ Health Survey [34]. The SF-12 data will be converted to SF-6D utility scores using an established algorithm [35,36]. The SF-6D provides a preference-based value of health benefits derived from standard questions, and a valid estimate of Quality Adjusted Life Years (QALYs) [37]. Change in QALYs will be used as an estimate of health benefit. In line with current theory and recommendations, participant-based production losses will not be included on the cost side of the analysis but (implicitly) counted within the QALY estimation [37,38].

### Theoretical mediators

The MobileMums program is grounded in Social Cognitive Theory and the intervention strategies target change in the specific theoretical constructs proposed [25], therefore the following five constructs are being evaluated as potential mediators via the self-administered questionnaire at each data collection point. *Physical activity barrier self efficacy* is assessed on a 5-point Likert scale (from 1 ‘not at all confident’ to 5 ‘very confident’), using a 12-item tool adapted from a previous scale [39]. Our version includes two additional items for postnatal women (i.e., I could exercise even when: ‘I don’t have anyone to look after the kids’; ‘I have housework to do’). This adapted version of the scale has demonstrated sensitivity to change among postnatal women [10,26] and had acceptable internal consistency (Cronbachs α = 0.71) [26]. *Outcome Expectancy* is measured using 10-item scale developed by Rodgers & Brawley [40]. Participants rate outcome likelihood (on a 10-point scale, 0–100% likelihood) and outcome value (on a 9-point scale, 1–9 importance) for seven physical activity outcomes and ratings are multiplied to indicate overall outcome expectancy (range 0–900). Consistent with the creator’s recommendations, the specific physical activity outcomes used in this study were determined from formative research with the target population. The most commonly reported positive (weight loss, improved fitness, more energy, less stress, improved mental well-being) and negative outcomes (injury, lose time to do other things) were included. Negative outcome expectancies were included because expectations are thought to be better predicted when both positive and negative outcomes are considered [41]. Our previous trial [26] and others [42] have demonstrated that the measure was sensitive to change in a physical activity intervention among postnatal women. The scale has acceptable internal consistency (Cronbachs α = 0.72) [26]. *Goal Setting Skills* are measured using the 10‒item Exercise Goal-setting Scale (EGS)[43]. This scale has good test retest reliability (r = 0.87) over an 8‒week period [43]. The EGS items assesses setting goals (e.g., I often set exercise goals), self-monitoring (e.g., I usually keep track of my progress in meeting my goals) and problem solving (e.g., If I do not reach my goals, I analyse what went wrong). Each item is measured on a 5-point Likert scale, but following our formative research with 12 postnatal women the original anchors (‘does not describe’ to ‘describes completely’) were found to be difficult to interpret so we adapted the EGS anchors to 1 ‘strongly disagree’ to 5 ‘strongly agree’. The adapted version of EGS had good internal consistency (Cronbachs α = 0.84) [26], similar to that of the original scale (r = 0.89)[43]. *Physical activity social support* from the participant’s partner (husband or defacto) and from their family or friends is assessed on a 5-point Likert scale using the Social Support for Exercise Scale [44]. Five items, including an additional one (‘offered to mind the kids so I could be more physically active’) are assessed on a scale from 1 ‘never’ to 5 ‘very often’. The original scale has good test-retest reliability (r = 0.55–0.79)[44], and this slightly modified version has demonstrated good internal consistency (Cronbachs α = 0.90) [26] and sensitivity to change among women with young children [10,26]. At T2 and T3 we included five additional items to specifically assess the support that participants received from their nominated MobileMums support person. *Perceived Environmental Opportunity for Exercise:* was measured using 12 items designed and implemented by Hoehner and colleagues [45]. These items were derived from a review of three commonly used questionnaires to assess environmental impact on physical activity participation [46], and are assessed on a five point Likert scale from 1 ‘strongly disagree’ to 5 ‘strongly agree’. Based on our formative research we added two additional items to the scale (‘There are footpaths wide enough to fit prams in my neighbourhood’; ‘Unattended dogs make it unsafe to walk in my neighbourhood’). The adapted scale has an acceptable internal consistency (Cronbachs α = 0.75) [26].

### Moderators

Demographic (e.g., age, number of children, employment status, education) and health-related (SF12v2™ Health Survey) [34] moderators were assessed in the self-administered questionnaire. Demographic questions follow the same format and response options used in the Census by the Australian Bureau of Statistics [47] to aid interpretation of representativeness of the sample.

### Sample size

Our sample size was based on the clinically meaningful increase in physical activity (assessed by the AWAS) observed in our pilot study (40 minutes/week) [27]. We chose to base the sample size on self-report physical activity data, not the objective accelerometer data, because our pilot data suggested the AWAS was likely to produce the higher sample size estimate due to larger variance. Using the variance observed in the self-report data of 102 minutes/week [27], and assuming 80% power and two-sided significance of 5% we needed 102 women per group. Estimating a 25% dropout, this figure was inflated to 128 per group, or 256 total.

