## Methods

### Study design

MobileMums is being evaluated in a 9-month, two-arm community-based randomised controlled trial. Participants are recruited on a rolling basis and randomly allocated to one of two study groups: the MobileMums intervention group or usual care control group. Data are collected before the program begins (T1), immediately post-intervention (T2, 3 months post baseline), and after a 6-month no contact maintenance period (T3, 9 months post baseline)*.* The final T3 data were collected in December 2012, and the trial is ongoing with further qualitative assessment of program impact. The trial was designed and will be reported in accordance with the CONSORT guidelines for reporting randomised controlled trials [28], and is registered with the Australian New Zealand Clinical Trials Registry (ACTRN12611000481976). Ethical clearance for this research was obtained through the Queensland University of Technology Human Research Ethics Committee.

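### The 25% dropout allowance multiplies 102 by 1.25 instead of dividing by 0.75, so on the plan's own completers-only calculation 128 per group gives about 77% power, not 80%

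*Protocol article*

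**What the plan says.** The Sample size section of the protocol article bases the trial on the self-report questionnaire (AWAS). It takes a difference of 40 minutes/week from the pilot study and describes the spread thus: "Using the variance observed in the self-report data of 102 minutes/week". It continues: "assuming 80% power and two-sided significance of 5% we needed 102 women per group". The dropout allowance follows directly: "Estimating a 25% dropout, this figure was inflated to 128 per group, or 256 total".

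The Study design section describes a "two-arm community-based randomised controlled trial", and the equal group sizes imply 1:1 allocation. No other section gives a different dropout rate or another derivation of 128.

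**The concern.** The section presents 102 per group as the number that must supply data and 128 as the number to randomise so that 102 remain after a quarter are lost. But 128 is what results from adding a quarter to 102. A 25% dropout removes a quarter of the women randomised, which is a larger number than a quarter of those needed at the end. So three of the section's statements do not fit together: 102 needed for 80% power, 25% dropout, and 128 randomised.

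What is at stake is the accuracy of the stated power for the outcome on which the trial was sized. Readers use that statement to judge how much a null or borderline AWAS result can rule out. The Background also gives the pilot's lack of power for minutes per week as one reason for running this trial.

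**Working it through.** **Inputs** (all from the Sample size section)

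- Difference to detect: 40 min/week.
- Spread: 102 min/week, called a variance in the text.
- Power 80%, two-sided 5%, so the normal quantiles are 1.960 and 0.842.
- Number needed before dropout: 102 per group.
- Dropout 25%; number after inflation: 128 per group, 256 in total.

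**Step 1. Reproduce the 102.** For two means with equal groups, n per group = 2 × (z for alpha + z for power)² × (SD / difference)². With the spread taken as a standard deviation:

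2 × (1.960 + 0.842)² × (102 / 40)² = 102.07 (unrounded quantiles).

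This matches the stated 102. Strict rounding up gives 103, a difference too small to matter. Read literally as a variance, 102 gives about 2 per group, and a one-sided 5% test gives 81. So the stated figure comes from a two-sided test with 102 min/week as the standard deviation.

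**Step 2. Reproduce the 128.**

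- Multiplying: 102 × 1.25 = 127.5, rounded up to 128. This is the plan's figure.
- Dividing: 102 / (1 − 0.25) = 136 per group, 272 in total. This is not the plan's figure.

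The gap is 136 − 128 = 8 per group, or 16 in total, which is too large to be rounding.

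**Step 3. What 128 leaves at 25% dropout.**

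128 × 0.75 = 96 per group, which is 6 fewer than the 102 required.

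**Step 4. Power with 96 per group, completers only.**

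- Standard error of the difference: 102 × √(2 / 96) = 14.72 min/week.
- 40 / 14.72 = 2.717, and 2.717 − 1.960 = 0.757, which gives 77.5% power (normal approximation).
- The t-test version gives 77.1%.
- For comparison, 102 per group gives 80.0% (normal) or 79.6% (t-test).

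**Step 5. Difference detectable with 80% power at 96 per group.**

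2.802 × 14.72 = 41.2 min/week, against the planned 40.

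**Step 6. Dropout rate that 128 can absorb.**

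1 − 102 / 128 = 20.3%. At 20% dropout, 128 × 0.80 = 102.4, so 102 are just retained.

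**The case against.** The strongest reply is that 77% is not the power of the planned analysis. The Data analyses section specifies intention-to-treat analysis, with multiple imputation that draws on a woman's previous responses through a random intercept. The Changes in physical activity section specifies a repeated-measures model fitted by generalised estimating equations. A woman lost before 9 months may still contribute baseline and 3-month data, so 25% dropout need not leave only 96 informative women per group. This stands. A reader might infer that imputation recovers nothing, or that the trial as analysed has 77% power. The document supports neither. Actual power depends on the within-woman correlation, on when women drop out, and on whether 102 is the standard deviation of a score or of a change, and none of these is given. Equally, the Sample size section does not use imputation or repeated measures to justify 128, so they do not repair the calculation as stated.

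A second reply is that the effect is small. That also stands. The detectable difference moves by about 3%, and a true standard deviation of 102 × √(96 / 102) = 98.95 min/week would offset the shortfall. The 102 is a pilot estimate whose precision is not stated.

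A reader might also infer that the shortfall undermines the Discussion's description of the sample as adequately powered. That remark concerns objective activity measures, whereas the 77% applies to AWAS self-report. The Sample size section says the AWAS was chosen because it was expected to need the larger sample, and the article gives no accelerometer standard deviation or difference. The calculation therefore does not contradict the remark.

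**Conclusion.** The dropout inflation is wrong as written. Under the stated 25% dropout, 128 per group does not retain the 102 women that the section says are needed; 136 per group would. On the section's own two-sample calculation with completers only, 96 per group gives about 77% power (77.1% by t-test, 77.5% by normal approximation), or 80% power for about 41 min/week. This rests on a 40 min/week difference, a standard deviation of 102 min/week, 1:1 allocation and a two-sided 5% test. It does not establish the power of the planned imputed, repeated-measures analysis, which cannot be computed from what is given.

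The loss of 2.5 to 3 power points does not invalidate the design, and no analysis or decision rule in the article turns on 128 versus 136. The point should be corrected but is not critical. Calling 102 min/week a variance is a separate slip of terminology: the units and the reproduced 102 show that a standard deviation was meant and used, so it adds nothing to the power shortfall.

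**What to change.** Restate the sample-size sentence so that power, dropout and number randomised agree. Suggested content:

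*With a standard deviation of 102 minutes/week, 128 women per group (256 in total) give 80% power to detect a difference of 40 minutes/week at two-sided 5% if dropout does not exceed about 20%. With 25% dropout, 96 women per group would remain, giving about 77% power for 40 minutes/week, or 80% power for about 41 minutes/week. These figures are for a two-sample comparison of completers.*

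The same edit replaces *variance* with *standard deviation*.

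The cost is wording only, with a slightly less favourable power statement. No added enrolment is proposed: the Study design section reports that the final 9-month data were collected in December 2012.

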### Data analyses

Data analyses will follow intention-to-treat principles [28], so all participants will be analysed according to their randomised group regardless of whether they complied with the program or not. Missing physical activity data will be imputed using a model that accounts for the often skewed distribution of physical activity. Missing data will be imputed using a regression model based on time and a subject’s previous responses using a random intercept. To account for the uncertainty in imputing missing data the analyses will use multiple imputation using the WinBUGS software. Statistical significance will be set to 5% and 95% confidence intervals will be given for all results.

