### Changes in physical activity

Changes in accelerometer-measured moderate-vigorous physical activity (minutes/week) and in AWAS planned moderate-vigorous physical activity and brisk walking (minutes/week) will be analysed using repeated-measures models. Preliminary descriptive analyses will consider the longitudinal trajectories of participants to determine the homogeneity of trajectories and identify outliers. We will fit the repeated measures models using a generalised estimating equations framework. Estimates of the main effects of time by intervention will be used to assess the impact of intervention on each outcome. Possible attrition bias will be assessed using a longitudinal model with a binary dependent variable of dropout at each assessment time. This model will include time-independent covariates such as age, and time-dependent covariates such as previous physical activity.

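### The stated imputation model does not list randomised group or group-by-time, so if followed as written it pulls the estimated effect on physical activity toward zero

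*Protocol article*

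**What the plan says.** Three statements in the protocol article matter here.

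- **Imputation model (Data analyses).** "Missing data will be imputed using a regression model based on time and a" subject's "previous responses using a random intercept". The section adds that the model will allow for skewness and that "the analyses will use multiple imputation using the WinBUGS software". Group is not among the listed terms, and nothing elsewhere in the article adds it or says that imputation is done by arm.
- **Analysis set (Data analyses).** Under intention to treat, "all participants will be analysed according to their randomised group regardless of whether they complied with the program or not". Group is used here to analyse women, not to impute their data.
- **Effect of interest (Changes in physical activity).** In a GEE repeated-measures model, "Estimates of the main effects of time by intervention will be used to assess the impact of intervention on each outcome". This covers accelerometer activity, AWAS planned activity and brisk walking.

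**The concern.** An imputation model should contain at least the terms that the analysis model estimates. Here the term of interest, group by time, is absent from the stated model that fills in the missing values. A woman who leaves before T2 contributes only a baseline value, which precedes randomisation. Given that value and time, her imputed follow-up values come from the same distribution in either arm. Averaging such women with the observed ones shrinks the estimated effect. This happens even when data are missing completely at random, and more imputations do not cure it.

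The rule covers missing physical activity data, so it touches every outcome used to answer the first research question. A real effect could be reported as smaller than it is, or missed, in a trial meant to decide whether further investment in the program is warranted.

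**Working it through.** **Inputs from the article.** Sample size section: effect 40 min/week, spread 102 min/week, 80% power, two-sided 5%, 25% dropout, 128 per group. Study design section: T1 baseline, T2 at 3 months, T3 at 9 months.

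**Assumptions not in the article.** Dropout is unrelated to outcome; dropouts share the full effect of 40; outcomes are normal; within-woman correlation is 0.3 to 0.7. The timing of dropout is not given, so two patterns are shown.

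**1. Reproduce the plan's figure.** n per group = 2 × (1.960 + 0.842)² × 102² / 40² = 2 × 7.849 × 10,404 / 1,600 = 102.07, against 102 stated. Then 102 × 1.25 = 127.5, rounded to 128. The 102 is called a variance, but its units and this result show that it works as a standard deviation.

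**2. T2 without group.** Let p be the share with no T2 value. Their expected imputed difference between arms is 0, so the estimate is (1 − p) × 40 + p × 0.
- All 25% leave before T2: 0.75 × 40 = 30, an attenuation of 25%.
- Half leave before T2: 0.875 × 40 = 35, an attenuation of 12.5%.

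**3. T3 without group.** Women lost between T2 and T3 have an observed T2 value that carries part of the effect, c. With equal correlation between visits, the weight on T2 given T1 and T2 is ρ/(1 + ρ). At ρ = 0.5 this is 1/3, so c is about 13 of 40. Simulation over ρ = 0.3 to 0.7 gave c of about 10 to 19.
- All leave before T2: 0.75 × 40 = 30.
- Half leave later: 0.75 × 40 + 0.125 × 0 + 0.125 × c = 31.25 (c = 10) to about 32.4 (c = 19).

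**4. Check by simulation.** 400,000 women, three visits, true effect 40 at T2 and T3. Imputation was by regression on previous responses or by a random-intercept model. Ranges are over both methods and all correlations, in min/week.

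| Dropout pattern | No group: T2 | No group: T3 | With group: T2 | With group: T3 |
|---|---|---|---|---|
| 25% before T2 | 29.3–30.6 | 29.4–30.8 | 39.5–40.8 | 39.5–40.6 |
| 12.5% before T2, 12.5% after | 34.9–35.4 | 31.2–32.5 | 39.5–40.2 | 39.4–40.7 |

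**5. Power, with all 25% missing at T2.** 1,500 simulated trials per setting, 128 per arm, 20 imputations, Rubin's rules.
- Baseline-adjusted analysis, outcome SD 102, correlation 0.5: 70% without group and 87% with it, a loss of 17 points.
- Change scores, SD of change 102, correlations 0.3 / 0.5 / 0.7: 58.1 / 58.3 / 56.0% without group and 81.1 / 80.5 / 77.3% with it, losses of 23.0 / 22.2 / 21.3 points.

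The like-for-like loss is therefore about 17 to 23 points. Comparing across correlations would stretch it to 25 (81 − 56). Neither analysis is the planned GEE, so the power levels are indicative only.

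**The case against.** **The article is condensed.** One sentence describes the imputation model. It does not say that the listed terms are the only ones or that the arms are pooled, and an analysis plan may add group. This stands as a limit, so the point is conditional on the model being followed as written. It does not remove the point. The sentence names predictors and random-effect structure, is not worded as a list of examples, and sits beside details of skewness and software. As stated, the model conflicts with the analysis model.

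**The error is conservative.** True: with no real effect, no false effect is created. But the trial also has to detect and size a real effect.

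**The size depends on assumptions.** Also true. If dropouts benefited less than completers, the true intention-to-treat effect is smaller and so is the attenuation. In the limit where they gain nothing, the true effect is 0.75 × 40 = 30 and the T2 estimate with all dropout before T2 would not be attenuated. The article does not offer such an assumption as its reason for the model.

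**Stronger readings that a reader might infer, and that the article does not support:**
- *The dropout model omits arm and so would hide differential dropout.* The text reads "This model will include time-independent covariates such as age, and time-dependent covariates such as previous physical activity". The covariates are given as examples, so arm is not excluded.
- *An observed T3 is ignored when T2 is missing.* A random intercept fitted jointly to all responses would be informed by T3, and the imputed T2 would carry part of the effect.
- *The diluted effect feeds the cost-effectiveness result.* The Cost-effectiveness sections take benefit from SF-12 data converted to SF-6D and model costs and QALYs. They do not name the activity effect as an input.

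**Conclusion.** The point holds in conditional form. The stated imputation model does not list the term that the analysis estimates and, if followed as written, biases the physical activity effect toward zero. The expected arm difference in imputed values is nil for women with baseline data only, and about 10 to 19 of 40 min/week at T3 for women who miss only T3.

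On the assumptions listed in the working, the bias is 5 to 10 min/week at T2 and about 7.5 to 10 at T3. The low end applies if half the dropout comes after T2, the high end if all of it comes before. The power loss applies only to the second case. The bias shrinks with less missing data. It should be settled before the physical activity outcomes are analysed.

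**What to change.** State in the analysis plan that the WinBUGS imputation model includes intervention group and group-by-time, or that imputation is done separately by arm, and that it uses all observed time points for each woman. Adding the randomisation stratum, or the other activity instrument as a predictor, is optional and not needed to remove this bias.

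The cost is one sentence and a few lines of model code. No new data are needed. The article reports that T3 collection ended in December 2012 but describes the analyses in the future tense, so the change can be recorded as a dated clarification before results by arm are examined.

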### Moderator analysis

Exploratory analysis of potential moderators will determine whether intervention effects differ across demographic (e.g., age, gender) and health-related (e.g., BMI, SF-12) characteristics. This analysis will be performed by considering the statistical significance of an interaction between a potential moderator and the intervention as part of the generalised estimating equations model.

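### The stated imputation model leaves out the moderators and their interaction with group, so exploratory RQ5 interactions are pulled toward zero, by about 15-25% at T3 with 25% dropout unrelated to the moderator

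*Protocol article*

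**What the plan says.** The Data analyses section gives the predictors of the imputation: "Missing data will be imputed using a regression model based on time and a subject’s previous responses using a random intercept". It adds that "the analyses will use multiple imputation using the WinBUGS software". It names no randomised group, moderator, interaction or demographic covariate.

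The Moderator analysis section describes RQ5: "Exploratory analysis of potential moderators will determine whether intervention effects differ across demographic" and health-related characteristics. The test is made by "considering the statistical significance of an interaction between a potential moderator and the intervention as part of the generalised estimating equations model".

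The section on changes in physical activity adds a dropout model: "Possible attrition bias will be assessed using a longitudinal model with a binary dependent variable of dropout at each assessment time". Of its covariates it says: "This model will include time-independent covariates such as age, and time-dependent covariates such as previous physical activity".

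The planned loss is in the Sample size section: "Estimating a 25% dropout, this figure was inflated to 128 per group, or 256 total".

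**The concern.** An imputation model should contain at least the terms that the analysis will estimate. Here the RQ5 analysis contains a moderator-by-group term that the stated imputation model implicitly sets to zero. A woman with no follow-up activity gets imputed values that do not depend on the combination of her group and her moderator level, so she pulls the estimated interaction toward zero. The combining rules for multiple imputation also assume that the two models agree. When they do not, the pooled standard error no longer describes the spread of the estimate.

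RQ5 is one of five research questions. In the patterns examined the error is toward the null: a real difference between subgroups would be understated and could be reported as absent.

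**Working it through.** **The plan's own figures.** The Sample size section uses a difference "observed in our pilot study (40 minutes/week") and a spread of 102 minutes/week. The text calls this a variance; it is read here as an SD. With 80% power and 5% two-sided significance, n per group = 2 × (1.96 + 0.84)² × 102² / 40² ≈ 102 (103 if rounded up), against 102 stated. Then 102 × 1.25 = 127.5, so 128 per group and 256 in total. The planned 25% is taken as the loss by T3.

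**Assumptions not in the document.** Balanced binary moderator; true interaction 40 minutes/week around a main effect of 40 (subgroup effects 20 and 60); equal correlation ρ between visits, 0.3-0.7; normally distributed activity; 20 imputations.

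**Expected shrinkage by arithmetic.** Let p2 be the share lost before T2 and p3 the share lost between T2 and T3.
- Women lost before T2 carry no interaction, so shrinkage at T2 = p2.
- Women seen at T2 and lost before T3 pass on part of it through their observed T2 value. With T1 and T2 both observed, the weight on T2 is w = ρ/(1+ρ).
- Shrinkage at T3 = p2 + p3 × (1 − w). At ρ = 0.5, w = 1/3.

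| Timing of the 25% loss (ρ = 0.5) | T3 by formula | Simulated T3 (ρ 0.3-0.7) |
|---|---|---|
| All before T2 | 0.25 = 25% | about 24-25% |
| 15% before T2, 10% after | 0.15 + 0.10 × 0.667 = 22% | 20-24% (split losses) |
| All between T2 and T3 | 0.25 × 0.667 = 17% | 14-18% |

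Simulated shrinkage at T2 was 13-18% with 12.5-15% missing, 23-25% with 25% missing, and nil with none missing. For the T2/T3 average it was 8-24%. The imputation was run both as sequential regression and as a random-intercept model. Rubin's rules were applied to the T1-adjusted interaction.

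**Dropout that differs by moderator level.** Take 15% lost before T2 and 10% after, with loss twice as common at the level with the smaller effect (multipliers 4/3 and 2/3).
- Effective loss at that level: 0.20 + 0.133 × 0.667 = 0.289. At the other level: 0.10 + 0.067 × 0.667 = 0.144.
- T3 interaction: 60 × 0.856 − 20 × 0.711 = 37.1, a shrinkage of about 7%. The simulation gave 6.6% at T3 and 5.7% at T2.
- With the heavier loss at the other level, the same arithmetic gives 60 × 0.711 − 20 × 0.856 = 25.6, or 36%. So the small figure depends on direction.

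**Is this only the missing group term?** With a true interaction of 40, 25% lost by T3 and dropout unrelated to the moderator, the T3 estimates were:

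| Imputation model | Estimate (true 40) |
|---|---|
| As stated | 30-34 |
| Plus group | 30-34 |
| Plus group, moderator and their product | 39-41 |

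Group alone gives every imputed woman in an arm the same average effect, so the interaction among imputed women is still absent.

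**Standard error.** Where the analysed visit had missing data, the Rubin SE was 1.15-1.35 times the true sampling SD (1.06-1.33 for the T2/T3 average), with coverage 97-99%. Example at T3 with ρ = 0.5 and all loss after T2: SD 19.9, Rubin SE 25.1, ratio 25.1/19.9 = 1.26; the complete-case SE was 25.7. At T3 and ρ = 0.5, power for the assumed interaction fell from about 0.34 to 0.14-0.23. With the full set of terms the SE ratio was 0.99-1.06.

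**The case against.** **The article is a condensation.** It does not say that its list of predictors is complete, it gives the moderators only as examples, and a fuller analysis plan could add terms. This stands as a caution. But the article does not leave the imputation model open: it states what the model is based on, and a reader who follows that text gets the shrinkage.

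**RQ5 is labelled exploratory, and power is low anyway.** This is true: about 0.34 for an interaction of 40 even in a complete-case analysis. It limits the importance of the point but does not make the stated procedure sound.

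**The size is conditional.** This is also right. It depends on how much dropout occurs, when, and in whom, none of which the document fixes.

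Some stronger readings are tempting and should not be drawn:
- That imputed women carry no moderation at all. This holds only for women with no observed follow-up; an observed T2 value carries part of it into T3.
- That the intervals are too wide in absolute terms. The SE is large only relative to the spread of the shrunken estimate; at about 25 it is no larger than the complete-case SE of about 25.7.
- That the plan expects its covariates to predict dropout. It only proposes to assess possible attrition bias. Of the two covariates it names, previous activity is already in the imputation, which leaves age.

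**Conclusion.** The point holds for RQ5. As written, the imputation omits the moderator and moderator-by-group terms that the Moderator analysis section estimates. At 25% dropout unrelated to the moderator, T3 interactions shrink by about 15-25%. The figure was about 6% in one scenario where dropout differed by moderator level, could be larger if the heavier loss falls on the more responsive subgroup, and is nil at a visit with no missing data. The reported SE overstates the spread of the shrunken estimate by about 15-35%. Adding randomised group does not cure this.

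These sizes rest on normally distributed outcomes, a binary moderator and a T1-adjusted interaction at T2, at T3 or for their average, rather than on the full GEE with a model for skewed activity.

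A reader might also infer that leaving out covariates biases the primary effect. That would need dropout to depend on a covariate differently in the two arms, and nothing in the document supports such a pattern, so no such claim is made. The absence of randomised group from the named predictors bears on RQ1 as a separate matter.

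**What to change.** For each RQ5 analysis, include in the imputation model randomised group, the baseline moderator being tested and the product of the two, one moderator at a time. An acceptable alternative for RQ5 is to fit the interaction to observed T2/T3 records adjusted for T1 activity, without imputation. Also add age as an imputation covariate, since the dropout model will examine it.

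Cost: a separate imputation run per moderator and slightly larger models for 256 women, using data already collected. The alternative without imputation is simpler, but it gives up protection where loss at T3 depends on activity at T2.
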